## Abstract

Data on the prevalence of most inborn errors of metabolism are still unavailable in Kazakhstan. The study aims to perform selective screening for hereditary metabolic diseases among patients aged from 1 day to 18 years in western Kazakhstan using the LC-MS/MS method, with establishing the reference values for the content of amino acids, acylcarnitines, and succinylacetone in blood samples of healthy children. Tasks: 1. To assess the burden of metabolic disorders detected by LC-MS/MS in western Kazakhstan by examination of children at clinical risk in pediatric clinics throughout the region; https://www.frontiersin.org/register?returnUrl=https://loop.frontiersin.org 2. To set the reference values of metabolites in the child population; 3. To analyze the age distribution, prevalence, and age of onset for each identified IEM, further comparing the obtained findings with those from previously published reports in other populations. Methods: To set the reference values of 51 metabolites in the child population, 750 healthy children will be included. The selective screening will be performed among 1,500 patients aged 1 day to 18 years with suspected hereditary metabolic disorders. Anticipated results: The results of selective screening will be interpreted by comparison with the reference values established. Diagnosis will be based on clinical signs, blood levels of amino acids, acylcarnitines, succinylacetone, and urine levels of organic acids and tests for gene mutations. An assessment of 37 inborn errors of metabolism frequencies in high-risk children will be performed. The research will further develop the national as selective as expanded newborn screening programs. The study was registered in clinicaltrials. gov (https://www.clinicaltrials.gov/study/NCT05910151) on 16 June 2023.

## 1 Introduction

Selective screening is an essential tool for diagnosing various types of inborn errors of metabolism (IEM). IEMs are a group of phenotypically and genotypically heterogeneous metabolic disorders caused by mutations in genes encoding enzymes of metabolic pathways or receptors. Deficiency or change in the activity of necessary enzymes or other proteins in intermediate metabolic pathways leads to the accumulation or deficiency of the corresponding metabolites in cells or body fluids, manifesting in a wide range of diseases with clinical heterogeneity, thus complicating their diagnosis (Mak et al., 2013). The classification of existing IEM is based on the biochemical properties of the substances involved (Han et al., 2015). Although these disorders are rare individually, they are numerous in the aggregate (Ozben, 2013). Many IEM do not have specific clinical signs and are difficult to diagnose using only clinical manifestations or routine laboratory tests (Champion, 2010). Most often, IEMs occur in early infancy and childhood, and the prevalence within different racial and ethnic groups is not the same. Hence, there are population differences in the incidence of IEM (Champion, 2010; Lampret et al., 2015; Shibata et al., 2018; Sarker et al., 2019). IEMs typically lead to irreversible neurological and psychological damage and/or disability or death in affected children. Early diagnosis of IEM can significantly reduce the risk of death and may prevent long-term neurological complications (Lampret et al., 2015; Dietzen et al., 2016). The purpose of NBS (newborn screening) is to presymptomatically identify infants with congenital conditions so that treatment can be started as early as possible and prevent or mitigate the long-term consequences of the condition. The expanded newborn screening program increased the screening panel of disorders from six (6) to more than twenty-eight (Pitt, 2010). IEMs represent the largest category of hereditary diseases amenable to causal therapy (van Karnebeek and Stockler-Ipsiroglu, 2014).

Selective IEM screening is usually performed for patients with clinical symptoms, positive results of routine laboratory tests, or having a family history suggesting a metabolic disorder. The methods most commonly used for metabolite detection have included gas chromatography-mass spectrometry (GC-MS) for organic acids, ion exchange chromatography-post column derivatization for amino acids (AAs), and, lately, liquid chromatography-tandem mass spectrometry (LC-MS/MS) for the analysis of AAs, acylcarnitines (ACs), and succinylacetone (SuAc) (Chace, 2009; Lampret et al., 2015; Gelb et al., 2022; Kaysheva et al., 2023). Currently, widely used technologies based on LC-MS/MS allow for simultaneously determining several metabolites, such as AAs, ACs, and SuAc, from a small amount of a biological sample (Gaugler et al., 2017). However, involved laboratories first should establish age reference cut-off ranges for each analyte for each population before patient screening/diagnosis, as cut-offs depend on various factors such as genetic background, geographic location of the population, diet, gender, age, etc. (Dietzen et al., 2016; Dogan et al., 2017; Yang et al., 2018; Sarker et al., 2019). The expansion of newborn screening beyond phenylketonuria (PKU) has occurred mainly due to the introduction of tandem mass spectrometry, which allows testing for multiple metabolic conditions from a single drop of blood (Kruszka and Regier, 2019).

At present, newborns are screened using LC-MS/MS as part of expanded newborn screening (ENBS) programs in most high-income and some low/middle-income countries (LMICs) (Sarker et al., 2019). Utilizing relatively simple tests, including detecting AAs, SuAc, and ACs in dry blood spots on filter paper, tandem mass spectrometry allows rapid screening and diagnosis of IEM (Han et al., 2015). The prognosis of patients with diseases targeted by ENBS has improved markedly in countries implementing the screening system (Therrell et al., 2014; Landau et al., 2017; Shibata et al., 2018). The NBS panels for each country, and sometimes for different regions within the same country, vary depending on the prevalence of each disorder in the population and the health system financing policy (Han et al., 2015; Hassan et al., 2016). Many LMICs do not yet have their national NBS programs. Meanwhile, local data on IEM incidence and outcomes can be used to persuade health officials to prioritize screening in healthcare expenses (Therrell and Padilla, 2018). Data on the prevalence of each IEM can serve as an essential tool to evaluate the cost-effectiveness of screening. Therefore, selective screening is the first step in projects to study the prevalence of IEM in developing countries experiencing economic difficulties. Developing countries face challenges in implementing and expanding their IEM screening programs, including financial issues, medical and logistical support, public education, policy development, program evaluation, and sustainability providing (Padilla et al., 2010; Hassan et al., 2016). LC-MS/MS can detect and quantify many metabolites in a single blood spot to diagnose amino acid disorders, organic acidemias, fatty acid oxidation disorders, and urea cycle disorders. MS/MS is expanding to implementing NBS programs for IEM and selective screening of children of different ages. The results from these expanded NBS programs provided information on the prevalence of these diseases in the United States (Therrell et al., 2014; Landau et al., 2017), some countries in Europe (Scolamiero et al., 2015; Messina et al., 2018; Lampret et al., 2020; Loeber et al., 2021), and Asia (Yunus et al., 2016; Dogan et al., 2017; Yang et al., 2020; Deng et al., 2021).

In Kazakhstan, MS/MS in metabolic screening programs is not yet developed due to the high cost of equipment and consumables and the lack of special screening centers and specialists. Data on the prevalence of most IEM, except phenylketonuria (Loeber et al., 2021), are still unavailable in Kazakhstan. The data obtained in this study can provide a comparative analysis of the prevalence of IEM in Asia and establish reference values for AAs, ACs, and SuAc concentrations in the blood of newborns in Kazakhstan. Reference interval data for acylcarnitines, succinylacetone, and amino acids obtained from the population of newborns in western Kazakhstan will be the first step in developing a national IEM diagnostic program.

The efficacy and risks of expanded newborn screening for IEM require careful evaluation before it can be accepted as a mandatory national program. The lack of epidemiological data on the incidence of IEM is one of the reasons for the delay in the development of proper population-based newborn screening for IEM using the LC-MS/MS method in Kazakhstan. Currently, NBS is being conducted in Kazakhstan for two hereditary diseases - phenylketonuria (PKU) and congenital hypothyroidism, the most represented screening diseases in most countries (Therrell and Padilla, 2018). This nationwide NBS program based on biochemical tests started in 2007 (Loeber et al., 2021), long after NBS was introduced in the United States in 1963 (Guthrie and Susi, 1963). Besides, in Kazakhstan, before the present study, state-funded MS/MS selective screening programs were implemented as sporadic pilot projects in some regions of the country without completion. Reports on these projects have not been published in peer-reviewed journals. As MS/MS neonatal screening is not mandatory in Kazakhstan, there are no uniform technical specifications for IEM screened by MS/MS in pilot studies. Hence, data on the frequency of IEM at the national level are not presented. For a country with no mandatory ENBS MS/MS program, selective screening can become essential for diagnosing IEM. The present research aims to develop and validate the LC-MS/MS method for simultaneously determining 51 metabolites in dry blood spots for IEM screening, as well as clarifying age-related ranges for AAs, ACs, and SuAc in Kazakhstan children. It is commonly accepted that children need to use reference populations that reflect changes associated with growth and development (Dogan et al., 2017). Therefore, one of the objectives of this study is to set reference intervals for the concentration of amino acids, succinylacetone, and acylcarnitines in dry blood spots for different age groups in the range from 1 day to 18 years. Owing to historically established social-cultural traditions supported by the legislation, consanguineous marriages are practically absent in Kazakhstan. This distinguishes Kazakhstan from many Asian and European countries, where consanguineous marriages are a real problem and, according to researchers, they are one of the reasons for the relatively high incidence of certain groups of IEM identified during selective newborn screening (Nagaraja et al., 2010; Al Riyami et al., 2012; Golbahar et al., 2013; Selim et al., 2014; Hassan et al., 2016; Demirelce et al., 2020; Gayduk et al., 2022; Magdy et al., 2022).

Accordingly, *the research hypothesis* is the following. Given the mentioned above social-cultural features of the Kazakh’s way of life, the obtained frequencies of different IEM are expected to be lower than in other countries practicing historically approved consanguineous marriages. Thus, *the study goal* is to perform selective screening for hereditary metabolic diseases among patients aged from 1 day to 18 years in western Kazakhstan using the LC-MS/MS method, with establishing the reference values for the content of amino acids, acylcarnitines, and succinylacetone in blood samples of healthy children.

Tasks:1. To assess the burden of metabolic disorders detected by LC-MS/MS in western Kazakhstan by examination of children at clinical risk in pediatric clinics throughout the region;2. To set the reference values of metabolites in the child population;3. To analyze the age distribution, prevalence, and age of onset for each identified IEM, further comparing the obtained findings with those from previously published reports in other populations.

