### 2.2 Selection of subjects

#### 2.2.1 Sample size estimation

When calculating the sample size for the upcoming project on selective screening, we relied on published similar studies. Researchers pointed out the following essential factors contributing to the sample size calculation: Daniel’s formula for prevalence studies in case of expanded screenings, the reported frequencies of different IEM within the studied populations, and the number of infants born in the country during the period of interest (Yoon et al., 2005; Golbahar et al., 2013; Hassan et al., 2016; Shibata et al., 2018; Sarker et al., 2019; Manta-Vogli et al., 2020). Notably, many researchers corrected their calculations, considering the situation with consanguineous marriages in their country.

According to the review by Shibata N et al., the IEM overall detection frequency was 3.0% (1.2% in Japan and 9.2% in other Asian countries) (Shibata et al., 2018). Yoon et al. reported 5.4% IEM among South Korean annual births (Yoon et al., 2005). Of these data on IEM frequency throughout Asian countries, Mongolian values (1.6%) have attracted our attention due to the similar nomadic history and way of life where consanguineous marriages were strictly forbidden (Shibata et al., 2018). Along with that, the Mongolian index does not include all types of IEM except the most distributed.

Based on mentioned factors, we requested data on the number of childbirths across the four provinces (oblasts) of western Kazakhstan within 3 years before the project started. The average rate of infants born alive annually ranged between 69–73,000 (https://stat.gov.kz/en/industries/social-statistics/demography/publications/). Thus, we have decided to build on the IEM average frequency of 2%–2.5% and determined the expected sample size of 1,500 children for selective screening with 750 healthy controls.

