#### 2.2.4 Criteria for inclusion in the selective screening for IEM

Children from 1 day to 18 years of age will be enrolled for selective screening for IEM if one of the main criteria or two or more additional criteria (symptoms) are identified. The inclusion criteria for IEM selective screening are presented in Table 2.

**TABLE 2 T2:** Criteria for inclusion in the selective screening for IEM.

Main criteria (symptoms)	Sudden deterioration in the clinical condition of the child after a period of normal development (days, weeks, months): Acute metabolic encephalopathy lethargy (coma) seizures resistant to antiepileptic therapy
	Hepatomegaly (hepatosplenomegaly)
	Metabolic acidosis with increased anion gap
	Multiple fractures
	Child mortality in the family from diseases with similar symptoms
Additional criteria (symptoms)	Treatment-resistant seizures
	Abnormal muscle tone: dystonia, hyperkinesis, hypotension
	Speech retardation
	Mental retardation of unknown cause
	Cardiomyopathy
	Tachypnea
	Frequent spitting up (vomiting)
	Osteoarticular anomalies (joint stiffness, chest deformity, rickets-like changes)
	Hernias (umbilical, inguinal-scrotal)
	Persistent or recurrent hypoglycemia
	Metabolic alkalosis
	An increase in ketone bodies in the blood and (or) urine
	Hyperammonemia
	An increase in the level of liver enzymes (ALAT, AST) more than 1.5 times
	Increase in the level of creatine phosphokinase (CPK) by more than 2 times
	Decrease in the level of alkaline phosphatase (AP) below the age norm
	Imaging or electrophysiological examinations indicating a metabolic disorder
	Leukopenia
	Thrombocytopenia
	Abnormal odor of urine, body, earwax, any unusual odor
	Hair growth disorders, alopecia
	Ophthalmic anomalies
	Unusual appearance, dysmorphic features
	History of death of a previous sibling of unknown cause
	Parents’ consanguinity
	Positive family history with metabolic disorders

Exclusion criiteria:

Patients having the following conditions will be excluded:1. Perinatal brain injury,2. Brain injury,3. Infections of the central nervous system,4. Toxicological diseases,5. Tumors,6. Chromosomal abnormalities,7. Symptoms specified in the Inclusion criteria, but with a confirmed diagnosis of any disease other than Amino acid disorders (AAD), Fatty acid oxydation disorders (FAOD), or Organic acidemias (OA).

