Indices of sensitivity (Sn), specificity (Sp), positive predictive values (PPVs), and negative predictive values (PVN) will be calculated for each diagnostic test under consideration. PPVs will be calculated by dividing the total number of true positive cases by the total number of true positive and false positive cases. The detection rate will be calculated by dividing the number of cases diagnosed by the number of screened children with suspected metabolic disorders. Multiple linear regression coefficients will be calculated to assess the relationship of each analyte with the factors of gender, weight, and place of residence. Due to the number of variables subjected to analysis, and the anticipated presence of multiple outcomes, the included tests may not be sufficient. So, the cluster analysis and, possibly, the decision-tree method will be applied. Decision trees break down complex data into more manageable parts, beneficial in prediction analysis, data classification, and regression. A dimensionality reduction method, principal component analysis (PCA), will also be applied. Two-sided levels <0.05 are assumed to be statistically significant. Statistical analysis will be carried out using the statistical packages IBM SPSS v. 23.0 (IBM, Armonk, NY, United States), Statistica (StatSoft, Inc., Tulsa, OK, United States, v. 10), and R 3.3.2 (R Foundation for Statistical Computing, Vienna, Austria.)

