Conducting ENBS and selective screening for IEM in Kazakhstan is of particular interest due to the entire absence of similar studies in the region of Central Asia, despite a significant number of studies conducted in neighboring areas (Russia, China, India, the Middle East, countries of East and Southeast Asia) (Guthrie and Susi, 1963; Nagaraja et al., 2010; Shibata et al., 2018; Therrell and Padilla, 2018; Yang et al., 2020; Deng et al., 2021; Loeber et al., 2021). A study by Shibata et al. revealed different rates of IEM incidence and spectrum of diseases in Asian countries. In addition, it was found that the ranges of IEM diseases determined using selective screening differed from those detected using ENBS (Shibata et al., 2018). For instance, the incidence of phenylketonuria in Asians (∼1:50,000 in Korea; ∼1:110,000 in Japan) is much lower than in Caucasians (∼1:10,000). The medium-chain acyl-CoA dehydrogenase (MCAD) deficiency, a common genetic metabolic disorder in Caucasian children with the A985G mutation of frequent occurrence, can serve as another example. Unlike Caucasians, MCAD is extremely rare in Korea and Japan (Vieira Neto et al., 2012). The frequencies (specific contribution to the IEM spectrum) of FAOD in the United States newborn population are, according to various studies, 45.2% in North Carolina (Frazier et al., 2006) and 38% in California (Feuchtbaum et al., 2012), which is slightly higher than in some European countries (Lindner et al., 2011; Shibata et al., 2018) and much exceeds the frequency of FAOD in Asian countries (Guthrie and Susi, 1963; Golbahar et al., 2013; Selim et al., 2014; Hassan et al., 2016; Shibata et al., 2018). FAOD detection rates for selective screening vary across countries, ranging from 0.29% in a South Korean study (Yoon et al., 2005) to 10.8% in a study in Oman (Al Riyami et al., 2012).

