Thus, the number of IEMs to be included in the protocol of the future ENBS in Kazakhstan through LC-MS/MS will depend, in addition to economic factors and laboratory equipment, on the frequency of diseases established during selective screening. In describing established cases of IEM, in addition to presenting the data specified in the Results section, the present study implies reflecting the family history of IEM, including the number of patients and families with IEM, gender, positive family history, consanguineous marriages, and age of the symptoms onset. Although, due to the historically and socially established forbiddance for consanguineous marriages in Kazakhstan, we assume their rare prevalence, the data obtained would be of interest for comparison with populations for which similar results are already available (Guthrie and Susi, 1963; Al Riyami et al., 2012; Golbahar et al., 2013; Hassan et al., 2016; Gayduk et al., 2022).

In the present study, the distribution of IEM primary clinical symptoms and their severity will be analyzed by age. Delayed diagnosis at an older age is commonly associated with many severe and irreversible clinical complications in patients (Champion, 2010; Selim et al., 2014; Han et al., 2015; Lampret et al., 2015; Dietzen et al., 2016). This circumstance calls for the urgent need for early detection and intervention to achieve favorable outcomes in IEM.

• Study limitations.1. The number of children with clinical manifestations to be examined in the ongoing screening for IEM by LC-MS/MS is limited.2. Other parts of Kazakhstan are not involved in the study. As such, assessing the differences between the levels of AAs, ACs, and SuAc in DBS of the child population and the differences in the IEM incidence appear impossible.3. The need for multiple and expensive tests to rule out rare and ultra-rare IEM.4. Metabolites for diagnosing other hereditary metabolic diseases, such as disorders of carbohydrate metabolism, disorders of porphyrin metabolism, disorders of purine and pyrimidine metabolism, disorders of steroid metabolism, disorders of mitochondrial function, disorders of peroxisomal function, and lysosomal storage disorders, are not included in this study.

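### Neither the detection rate nor the birth-based incidence can attribute a lower IEM frequency to marriage custom, because both depend on which children are referred

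*Protocol article*

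**What the plan says.** Section 1 labels one statement as the research hypothesis: "the obtained frequencies of different IEM are expected to be lower than in other countries practicing historically approved consanguineous marriages". It names the cause in advance: "Given the mentioned above social-cultural features of the Kazakh’s way of life". The preceding paragraph describes consanguineous marriage as practically absent in Kazakhstan. Task 3 plans "further comparing the obtained findings with those from previously published reports in other populations".

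Two measures are available for that comparison:

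- **Detection rate (section 3.2).** "The detection rate will be calculated by dividing the number of cases diagnosed by the number of screened children with suspected metabolic disorders".
- **Birth-based incidence (sections 3.4 and 4).** Cases are related to children born in western Kazakhstan in 2023–2024. Section 4 would set the resulting frequencies against incidence data from elsewhere in the world.

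Children reach the study by clinician referral on symptoms (section 2.2.2). Table 2 admits a child on any one of five main criteria or any two of 26 additional ones. The additional criteria include non-specific signs such as tachypnea, hernias and speech delay, and also "Parents’ consanguinity". The four numbered limitations in section 4 do not mention referral selection.

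**The concern.** The hypothesis is a contrast between countries with a cause attached. The data are a symptom-selected sample from one region, and the comparators are published reports. The protocol does not require those reports to share its entry rule, age range or disease panel. Nor is there a useful contrast inside the study, since the protocol itself expects consanguinity to be rare.

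A difference from another country could therefore come from marriage custom, from referral practice, or from both, and the design cannot tell them apart. This has consequences beyond the paper: section 4 says the choice of disorders for a future national newborn panel will depend partly on the frequencies found here.

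**Working it through.** The plan gives no figure for the cross-country comparison that could be reproduced. The check is how each measure responds to referral when disease frequency is held fixed.

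**Inputs from the protocol.** 1,500 screened children; planning frequency 2%–2.5%; 69,000–73,000 live births a year; published detection frequencies of 3.0% overall and 9.2% in Asian countries other than Japan (all section 2.2.1). **Assumptions.** The planning frequency is read as the expected detection rate. Two full years of births are used. The referral multipliers are illustrative, because the documents give none.

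**1. Formulas.** Let f be the true disease frequency in a child population of size P, s the share of true cases that are referred and found, N the number of children referred, and B the number of births.

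- Cases found = s × f × P.
- Detection rate = s × f × P / N = f / b, where b = (N/P)/s is referral breadth.
- Birth-based incidence = s × f × P / B.

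Both measures rise and fall with f, but neither isolates it. If breadth here is k times that of the comparator, the ratio of detection rates is (ratio of f) / k.

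**2. Plan's own scale.** 1,500 × 2.0% = 30 cases; 1,500 × 2.5% = 37.5 cases.

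**3. Same disease frequency, different breadth.** The expected detection rate is the comparator rate divided by k:

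| Assumed k | From 3.0% | From 9.2% |
|---|---|---|
| 1.25 | 2.4% | 7.4% |
| 1.5 | 2.0% | 6.1% |
| 2 | 1.5% | 4.6% |
| 4 | 0.75% | 2.3% |

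Narrower referral acts the other way. If the same 30–37.5 cases were found in 750 children, the rate would be 4.0%–5.0%. That assumes no case is lost by halving referrals, which is the extreme case.

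**4. Hiding a real difference.** If f here is half the comparator's and breadth is also half, the ratio is 0.5 / 0.5 = 1. A true halving would not be seen.

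**5. Against sampling error.** At 2.25%, the 95% half-width is 1.96 × √(0.0225 × 0.9775 / 1,500) = 0.75 percentage points, an interval of about 1.5% to 3.0%. A two-fold change in breadth moves the expected rate to 1.125% or 4.5%, outside that interval. The confidence interval does not cover this uncertainty.

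**6. Birth-based incidence.** Two years give 138,000–146,000 births. 30/146,000 = 20.5 per 100,000 (1 in 4,867); 37.5/138,000 = 27.2 per 100,000 (1 in 3,680). The figure moves in proportion to s: if half as many of the true cases reached referral, it would be 10.3–13.6 per 100,000. The numerator can include a child of any age up to 18, while the denominator holds only children born in 2023–2024, so most eligible birth years are missing from it.

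**7. Opposite directions.** Suppose referral doubles from 1,500 to 3,000 children and finds 1.5 times the cases, 45 instead of 30. The detection rate falls from 2.0% to 1.5%. The birth-based figure over 146,000 births rises from 20.5 to 30.8 per 100,000. The same change in practice favours the hypothesis on one measure and counts against it on the other.

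**The case against.** The protocol's goal, tasks and primary outcomes are largely descriptive. No test or endpoint is tied to the hypothesis, so it is not certain that a low rate would be credited to marriage custom. Section 4 also concedes that a thorough assessment of prevalence needs expanded newborn screening, and reports that selective and newborn screening find different ranges of disease. All of this stands and limits the point to what may be concluded. It does not remove it, because the hypothesis names its cause and the comparison is planned.

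Several stronger readings are tempting but not supported:

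- **That the hypothesis is confirmed before data are seen.** The planning value of 2%–2.5% is below 9.2%, but the 9.2% group is not identified as countries practising consanguineous marriage. The planning value also lies above the cited rates for Japan (1.2%) and Mongolia (1.6%).
- **That the cited spreads prove a referral artefact.** The rates differ 7.7-fold overall (9.2/1.2). For fatty acid oxidation disorders, "FAOD detection rates for selective screening vary across countries, ranging from 0.29% in a South Korean study" to 10.8% in Oman, the spread is 37-fold. The protocol attributes neither to referral, and section 1 cites the Oman study among those linking consanguinity to higher incidence. That end of the range fits the hypothesis equally well.
- **That the results would not depend on true disease frequency.** They would; it is confounded with referral, not absent.
- **That the consanguinity entry criterion distorts the sample materially.** It is one of 26 additional criteria, two are needed, and the protocol expects such marriages to be rare. Its effect is probably small.

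**Conclusion.** The concern holds as a limit on inference. The detection rate confounds disease frequency with referral breadth. The birth-based incidence confounds it with completeness of referral and also mixes birth cohorts. Neither can attribute a difference between countries to marriage custom.

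The size of the bias cannot be estimated from the documents, and its direction is not fixed. Under assumed multipliers of 1.25 to 4, an unchanged disease burden gives a detection rate between 80% and 25% of the comparator's; a multiplier of 2 halves it. Multipliers below 1 raise it. The conclusion does not rest on any particular multiplier, only on referral practice being able to differ between programmes and on nothing in the protocol controlling for that.

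**What to change.** 1. In section 1, replace the hypothesis with a descriptive aim: to estimate the proportion of referred children in western Kazakhstan in whom an IEM is confirmed, with a 95% confidence interval. Make no causal attribution to consanguinity.
2. Limit cross-country comparison of detection rates to other selective-screening programmes. Show entry criteria, age range and disease panel beside each rate.
3. In sections 3.4 and 4, do not match the birth-based figure with newborn-screening incidence as if the two were equivalent. State that its numerator comes only from referred children of all ages.
4. Add referral selection to the limitations in section 4, noting that it can act in either direction.
5. Report consanguinity among confirmed cases, as section 4 already plans. Extend this to all 1,500 children only if the registration card records it; the card is not shown in the article.

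The cost is rewording and a few columns in a comparison table. Some published programmes may not report their entry criteria, which would shorten the list of usable comparators. The main downside is that the paper could not present a lower rate as support for the marriage-custom hypothesis.
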